### Concomitant or Rescue Medication

The investigators monitored the participants for any concomitant or rescue medication required during the study period. In the event of any AEs or an increase in pain intensity, rescue medication was permitted at the investigators’ discretion. All instances of concomitant care were carefully documented in the CRF.

### Outcome Measures

The primary outcome was the change in the Western Ontario and McMaster Universities Osteoarthritis Index (WOMAC) score from baseline. The secondary outcome measures included the change in the score for pain, stiffness, and physical function from baseline (assessed using the WOMAC scale); the change in range of motion of the knee joint (assessed using a goniometer); the change in the scores of the numeric pain rating scale, Pain Disability Index, and 12-item short-form survey questionnaire (to assess health-related quality of life); the change in high-sensitivity C-reactive protein and interleukin-6 levels, MRI findings (to assess knee structural changes), and dual-energy x-ray absorptiometry scan findings (to assess change in bone mineral density); and the change in the need for rescue analgesic medication.

The outcomes were evaluated every 30 days until day 180 from baseline. Laboratory investigations were conducted at baseline and on day 180.

### Safety Assessment

The safety of the trial interventions was determined by recording the incidence of AEs, if any, during scheduled follow-up visits using a structured format. All AEs during the study were recorded and monitored in accordance with the International Council for Harmonisation–Good Clinical Practice (GCP) guidelines. Safety was also evaluated by performing liver function tests (LFTs) and kidney function tests (KFTs) on days 90 and 180 from baseline.

### Sample Size

On the basis of the results from a previous study [11], in which the difference in WOMAC score between the Ayurveda and conventional group after 12 weeks of treatment was 24 points, this study has been designed to have 80% statistical power to detect a difference of at least a 20-point improvement (change from baseline) in the WOMAC score after treatment between the 2 groups (pooled SD 42; 2-sided *t* test, α=.05). To achieve this, 69 participants per group were required. Accounting for an expected attrition rate of 10%, the final sample size for each group was determined to be 75 participants (150 in total).

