The present RCT protocol has several key strengths. First, it uses a complex Ayurveda regimen that incorporates therapeutic procedures and internal medications, which are easy to administer, well-tolerated, and safe, with the potential to address osteoarthritis-related pathological changes. Second, the study includes an adequate sample size and validated subjective assessment tools, along with imaging and relevant biomarkers as outcomes to address various parameters related to the pathogenesis of osteoarthritis.

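### 75 per group less the stated 10% attrition leaves 67.5, not the 69 the plan says it needs: a minor arithmetic slip in the sample size paragraph

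*Protocol article*

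**What the plan says.** The Sample Size section of the protocol article gives every input. The target is stated as "this study has been designed to have 80% statistical power to detect a difference of at least a 20-point improvement" between groups, with a pooled SD of 42 and the test given as "2-sided *t* test, α=.05". The section then says "To achieve this, 69 participants per group were required". The last step reads: "Accounting for an expected attrition rate of 10%, the final sample size for each group was determined to be 75 participants (150 in total". The Randomization section gives 1:1 allocation. The Discussion later lists as a strength that "the study includes an adequate sample size".

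Two other sections determine how many participants reach the analysis. Statistical Methods plans a modified intention-to-treat analysis that imputes missing values by last observation carried forward (LOCF) for anyone with at least one visit after baseline. The section on compliance says that data collected before withdrawal will be used.

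**The concern.** Two adjacent sentences cannot both be right. If 69 per group must remain after 10% attrition, 75 is too few; if 75 is the intended number, fewer than 69 remain. The 69 also looks slightly low for the test named. Both steps err in the same direction, towards a smaller trial. The planned size and power support the article's claim of an adequate sample, and any reader can check the attrition step with one multiplication. What is at stake is the accuracy of a published design figure, and a small amount of power if the expected dropouts really are lost to the analysis.

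**Working it through.** **Inputs (all from Sample Size):** difference 20, SD 42, two-sided alpha 0.05, power 80%, 69 required per group, attrition 10%, 75 per group randomised.

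**1. Reproducing the 69.** The normal formula is n = 2(z₀.₉₇₅ + z₀.₈₀)² SD²/difference². With numbers, n = 2 × (1.95996 + 0.84162)² × 42²/20² = 69.23. The plan's 69 is this value rounded to the nearest integer; rounded up, as is usual for a required size, it is 70.

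**2. The test actually named.** For a two-sample t test with n per group, power comes from the noncentral t distribution with 2n − 2 degrees of freedom and noncentrality 20/(42 × √(2/n)).

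| n per group | Power, t test | Power, normal |
|---|---|---|
| 67.5 (67 + 68) | 78.4% | 79.0% |
| 69 | 79.3% | 79.9% |
| 70 | 79.9% | 80.4% |
| 71 | 80.4% | 81.0% |
| 75 | 82.6% | 83.1% |

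The smallest n that reaches 80% with the t test is 71.

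**3. Attrition step, from the plan's own 69.**
- Randomise 75, lose 10%: 75 × 0.90 = 67.5 per group, 135 in total, which is 1.5 per group below 69.
- To keep 69: 69/0.90 = 76.7, so 77 per group (154 in total).
- The common shortcut, 69 × 1.10 = 75.9, rounds to 76. It yields 75 only if truncated.
- Attrition that 75 can absorb: (75 − 69)/75 = 8.0%.

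**4. Both steps together.** From 71: 71/0.90 = 78.9, so 79 per group (158 in total), 4 per group above 75.

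**5. Consequence.**
- All 10% lost to the analysis (67 + 68): power 78.4% for 20 points; the difference detectable with 80% power is 20.4 points.
- All 150 analysed: power 82.6% for 20 points, if the SD of 42 also applies to carried-forward values (an assumption; the article does not address it).

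**6. Sensitivity to the printed SD.** The SD is given as a whole number. At 41.5 the normal formula gives 67.6, and at 42.5 it gives 70.9. At 41.5 to 41.6 the t test itself needs only 69. The gap between 69 and 71 is therefore within the precision of the printed input. The attrition step does not depend on the SD.

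**The case against.** A reader might infer that the trial does not deliver its stated 80% power. The documents do not support that as a flat statement. It assumes that every dropout leaves the analysis, whereas Statistical Methods keeps, through LOCF, anyone seen at least once after baseline, and the compliance section uses data up to withdrawal. Only participants with no follow-up visit at all are lost. On the plan's inputs, 71 analysed per group gives 80.4%, so power falls below 80% only if 5 or more of 75 per group have no visit after baseline. The abstract also reports that all participants completed the study. If that is literal, 75 per group are analysed and power is 82.6%; if it means only that follow-up has ended, the LOCF point still applies. All of this rests on the SD of 42 holding for imputed values.

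It can also be said that 69 against 70 or 71 is rounding and approximation, that the worst case is only 1.6 percentage points below target, and that recruitment is over. These points stand, and they make the matter minor. The worst case does not overturn the article's description of the sample as adequate.

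None of this makes 75 follow from 69 and 10%. The Sample Size section makes its own attrition allowance and does not appeal to LOCF to justify it.

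A further tempting step is to say that a baseline-adjusted analysis would bring power back above 80%. The article gives no correlation between baseline and change, so that claim has no input to rest on.

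**Conclusion.** The sample size paragraph is wrong as written, and the error is minor. The firm part is the attrition step: 10% off 75 leaves 67.5 per group, against a stated requirement of 69, which would need 77. The gap is 2 per group (4 in total) and does not depend on any assumption beyond the plan's own figures. The secondary part, that 69 should be 70 or 71, holds only if the SD is exactly 42.

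The effect on power depends on who is analysed: 78.4% if 10% have no analysable outcome, and 82.6% if all 150 are analysed, with other losses up to 10% in between. The upper figure assumes that the SD of 42 applies to LOCF values.

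**What to change.** Restate the paragraph, with no added enrolment and no change to the design. Suggested content: 75 participants per group were randomised. If 10% have no analysable outcome (about 135 analysed), power is about 78% for a 20-point difference, or 80% for 20.4 points. If all 150 are analysed under the modified intention-to-treat approach with LOCF, power is about 83%, assuming an SD of 42 for imputed values.

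If the 69 is kept as the historical figure, note that it is the normal-approximation value of 69.23 rounded down, and that 10% attrition from 69 corresponds to 77 per group. Make no claim about power gained by baseline adjustment unless a baseline correlation is stated.

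The cost is one corrected paragraph, best made before results are reported, and a power figure that is slightly less favourable in the case where dropouts are lost.

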### Recruitment of Study Participants

During the study, the investigators screened individuals with clinical features of osteoarthritis of the knee who visited the outpatient department of the study sites, based on the defined inclusion and exclusion criteria, to identify and recruit potential individuals. The research personnel allocated the eligible participants to either of the 2 groups based on a computer-generated randomization schedule (Figure 1). The screening process was continued until the target sample size for the study was achieved.

**Figure 1 figure1:**
[figure not shown]
The study schedule. BMD: bone mineral density; BP: blood pressure; CBC: complete blood count; CRF: case record form; DEXA: dual-energy x-ray absorptiometry; ECG: electrocardiogram; ESR: erythrocyte sedimentation rate; HbA1c: hemoglobin A1c; hs-CRP: high-sensitivity C-reactive protein; IL-6: interleukin 6; KFT: kidney function test; LFT: liver function test; MRI: magnetic resonance imaging; RA: rheumatoid arthritis; SF-12: 12-item short-form survey; WOMAC: Western Ontario and McMaster Universities Osteoarthritis Index.

### Randomization

The eligible individuals were randomly assigned to the Ayurveda group or the control group with a 1:1 allocation. SPSS software (version 15.0; IBM Corp) was used to generate the random number sequences. The randomization sequence was generated by an independent statistician who was not involved in participants’ enrollment and assessment.

### Allocation Concealment

Sequentially numbered, opaque, sealed envelopes were used to ensure allocation concealment. The participant’s enrollment number was printed on the top of the envelope, and a slip indicating the participant’s allocated group was placed inside. After completing all baseline assessments, the research staff provided the sealed envelope to the eligible individuals. The individual opened the envelope and was then allocated to a group as indicated on the slip inside. The opened envelope and the printed slip were attached to the participant’s CRF for documentation and trial monitoring.

### Data Collection

The baseline demographics, clinical, and physical examination data were collected by qualified Ayurveda study personnel and recorded in a CRF designed for this purpose. The subjective and objective outcome assessments were conducted according to the study protocol. Knee pain, stiffness, and functional disability were assessed using the WOMAC score [38]. The self-reported severity of pain was recorded using a numeric pain rating scale and Pain Disability Index [39,40]. The overall quality of life was assessed using a validated scale, the 12-item short-form survey questionnaire [41]. These outcomes were assessed at baseline and during follow-up visits on days 30, 60, 90, 120, 150, and 180.

Serum samples for the objective assessment parameters, such as proinflammatory biomarkers, LFT, and KFT, were collected at baseline and on day 180 (LFT and KFT were also assessed on day 90), and transported to the NABL-accredited laboratory, along with data from MRI and dual-energy X-ray absorptiometry scans. The data received from the laboratory were entered in the CRF and e-CRF. The research team underwent training on the study protocol and standard operating procedures for the study conduct, storage and dispensing of study interventions, handling of biological samples, data collection, and data recording to ensure compliance with GCP principles, while ensuring participant safety, data accuracy, and reliability.

### Data Management

Data management in this clinical study adhered to stringent guidelines to ensure the accuracy, reliability, and integrity of the collected information. Upon the participant’s assessment, the research team promptly entered the data into CRFs and e-CRFs. Source documents and CRFs were securely stored in restricted-access areas, limited solely to the study team. Electronic CRFs were password-protected and stored in secure, access-restricted computer systems.

The data entered by the study personnel underwent meticulous cross-verification by the study investigators at the study site, ensuring the reliability of the data. Rigorous quality measures were implemented, such as regular audits, to identify and address any discrepancies in the data. Data management practices adhered to regulatory guidelines and ethical principles, prioritizing the protection of participant rights.

### Statistical Methods

Categorical data will be presented as numbers (percentages) and compared between groups using the chi-square test. Continuous data following normal distributions will be reported as mean (SD), and between-group comparisons will be performed using the independent sample *t* test. Within-group comparisons for normally distributed data will be conducted using the paired sample *t* test or repeated measures ANOVA. Nonnormally distributed data will be reported as median (first and third quartiles), and between-group comparisons will be performed using the Mann-Whitney *U* test. Within-group comparisons will be conducted using the Wilcoxon signed rank test or the Friedman test. A *P* value <.05 will be considered statistically significant. SPSS software (version 29.0; IBM Corp) will be used for statistical analysis.

The modified intention-to-treat analysis approach will be applied to handle missing data. Missing data for all participants with available data from at least 1 visit after baseline (day 30) will be imputed. The last observation carried forward method will be used to impute the missing values.

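### The groups are compared on WOMAC change without baseline adjustment, by a t test or Mann-Whitney test chosen on the observed distribution; this is valid but gives up precision and leaves the estimand open

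*Protocol article*

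**What the plan says.** Outcome Measures defines the endpoint: "The primary outcome was the change in the Western Ontario and McMaster Universities Osteoarthritis Index (WOMAC) score from baseline". Sample Size powers it as a mean difference, with "80% statistical power to detect a difference of at least a 20-point improvement (change from baseline) in the WOMAC score" between the groups, and gives "pooled SD 42; 2-sided" t test at the 5% level.

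Statistical Methods does not name a test for the primary outcome separately. It gives a general rule for continuous data: "Continuous data following normal distributions will be reported as mean (SD), and between-group comparisons will be performed using the independent sample" t test; and "Nonnormally distributed data will be reported as median (first and third quartiles), and between-group comparisons will be performed using the Mann-Whitney" U test. Repeated measures ANOVA appears only among the within-group comparisons. No covariate-adjusted model and no longitudinal model comparing the groups is named. That the primary comparison is an unadjusted test on change therefore follows from these three sections read together.

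Data Collection schedules WOMAC at baseline and at six follow-up visits, days 30 to 180. Allocation Concealment has all baseline assessments completed before the envelope is handed over. Baseline WOMAC is thus a covariate that allocation cannot have influenced.

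**The concern.** Three features of the stated method are weak.

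- **No baseline adjustment.** A change score subtracts the whole baseline value. When the baseline/follow-up correlation is below 1 and the variances are equal, that over-corrects for a chance baseline difference and adds noise. ANCOVA subtracts only the part of baseline that predicts follow-up.
- **Follow-up visits unused between groups.** Repeated measurement enters only the within-group tests, which do not address the randomised comparison.
- **Test chosen by the data.** The distribution found decides both the summary (mean or median) and the test. If Mann-Whitney is triggered, the main result no longer estimates the mean difference for which the trial was sized. With about 70 per arm, a t test or ANCOVA tolerates moderate skew, so the switch buys little.

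At stake are the precision of the primary estimate and whether its target is fixed in advance. Recruitment is complete, so the analysis is the only remaining place to gain precision.

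**Working it through.** **Inputs from the article.** Difference 20, SD 42, two-sided 5%, 80% power (Sample Size). Of the numbers, "69 participants per group were required", and then: "Accounting for an expected attrition rate of 10%, the final sample size for each group was determined to be 75 participants (150 in total"). Randomisation is "with a 1:1 allocation".

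**Assumptions not in the article.** SD 42 is the SD of change, since the effect is expressed as change. The baseline/follow-up correlation r is 0.3 to 0.7. Baseline and follow-up variances are equal, except where varied in step 4.

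**1. The plan's own figure.** n per group = 2 × [42 × (1.960 + 0.842) / 20]² = 69.2. The stated 69 is this rounded down; the exact t calculation gives 71. For attrition, 69 / 0.9 = 76.7 and 69 × 1.1 = 75.9, against the stated 75. The sample size reproduces to within two participants at each step. Losing 10% of 150 leaves 135, that is 67 + 68.

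**2. Unadjusted power (noncentral t).**
- 67 + 68: SE = 42 × √(1/67 + 1/68) = 7.23; 20 / 7.23 = 2.77; power 78.4%.
- 75 + 75: SE = 42 × √(2/75) = 6.86; 20 / 6.86 = 2.92; power 82.6%.

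The second case matters because the article carries forward the last observation for anyone with at least one post-baseline visit. The number analysed therefore lies between these two. The 82.6% assumes that the SD stays at 42 under that imputation.

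**3. Baseline-adjusted power, equal variances.** With score variance s², Var(change) = 2(1 − r)s² and the ANCOVA residual variance is (1 − r²)s². The ratio is (1 + r)/2, so the adjusted SD = 42 × √((1 + r)/2). One further degree of freedom is used.

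| r | Adjusted SD | Power, 67 + 68 | Power, 75 + 75 |
|---|---|---|---|
| none (unadjusted) | 42.0 | 78.4% | 82.6% |
| 0.3 | 33.9 | 92.6% | 94.9% |
| 0.4 | 35.1 | 90.7% | 93.4% |
| 0.5 | 36.4 | 88.7% | 91.7% |
| 0.6 | 37.6 | 86.7% | 90.0% |
| 0.7 | 38.7 | 84.6% | 88.1% |

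At r = 0.5 the variance ratio is 0.75, worth 1/0.75 = 1.33 times the participants.

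**4. Unequal variances.** If follow-up SD is k times baseline SD, the ratio is k²(1 − r²) / (1 + k² − 2rk).
- k = 1.2, r = 0.7: 0.734 / 0.760 = 0.966; adjusted SD 41.3; power 79.8% with 67 + 68.
- k = 1.5, r = 0.5: 1.688 / 1.750 = 0.964; adjusted SD 41.2; power 79.9%.

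Both still exceed the unadjusted 78.4%, but by little more than one point.

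**5. If SD 42 is the SD of the score instead.** With 67 + 68, the unadjusted change test against ANCOVA gives 64.1% against 82.1% at r = 0.3, 78.4% against 88.7% at r = 0.5, and 94.4% against 97.0% at r = 0.7. ANCOVA stays ahead, but the size of the gain differs greatly.

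**6. Chance imbalance.** Take r = 0.5; an SD of change of 42 then implies a score SD of 42. A baseline difference at the 95% limit of chance is 1.96 × 42 × √(2/75) = 13.4 points. The change-score estimate moves by (1 − r) × 13.4 = 6.7 points, a third of the 20-point target.

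**7. Mann-Whitney branch.** On normal data its efficiency is 0.955. Power at 67 per group is then about 76.8% against 78.7% for the t test (both normal approximation). The loss of power is small; the change of estimand is the larger issue.

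**The case against.** The strongest reply is that this is a matter of efficiency and not an error. Under randomisation the unadjusted t test on change has the right type I error and is unbiased. Regression to the mean acts on both arms alike in expectation, and chance imbalance is already reflected in the standard error. All of that stands. The imbalance argument concerns the one estimate this trial will produce, conditional on the imbalance it happens to have.

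A reader might infer that the trial is underpowered and that adjustment would restore the planned 80%. The article does not support that. The shortfall is below two points with 67 + 68 analysed, and it disappears (82.6%) if the carry-forward rule keeps all 75 per arm at the same SD. Nor can one say that adjustment takes power above 80% whatever the data: r is not given, the variances may differ, and the SD is not labelled as that of change or of score.

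It can also be said that covariates and longitudinal models are usually left to the analysis plan. That is fair for what the article omits, and for whether randomisation was stratified, on which it is silent. It does not protect what the article states, namely an unadjusted test and a switch driven by the observed distribution.

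Finally, the change cannot be called free. The Results section says analysis is in progress, so a new primary model is a late change in an open-label trial.

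**Conclusion.** The point holds as a recommendation to improve the stated analysis, not as a finding that the planned t test is invalid. Baseline adjustment gains precision without new data and removes the effect of chance imbalance in baseline WOMAC. Fixing the mean difference as the target removes the dependence on a normality check.

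Under the assumptions listed, the gain runs from about 14 points of power at r = 0.3 to about 6 at r = 0.7, whether 67 + 68 or 75 + 75 are analysed (14.2 to 6.2, and 12.3 to 5.5). It can fall to little more than one point if follow-up variance exceeds baseline variance. The direction is secure; the size is not.

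All figures are for the superiority comparison used in Sample Size. Study Design and Setting calls the trial noninferiority, and these figures do not address that label.

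**What to change.** Before the analysing statistician, whom Limitations describes as blinded, sees allocation, issue a dated amendment with these terms:

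- **Primary analysis:** ANCOVA of WOMAC on treatment and baseline WOMAC, at a named time point. The corresponding contrast from a longitudinal model over the follow-up visits is an alternative; it would replace last observation carried forward for this outcome, and the amendment should say so.
- **Reporting:** adjusted mean difference with 95% CI, whatever the normality check shows.
- **Sensitivity:** the unadjusted t test and the Mann-Whitney test.
- **Continuous secondary outcomes:** the same adjustment, each for its own baseline value.

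The cost is one degree of freedom and a late, but blinded, change to the plan, which the report should disclose with its date. No new data are needed. If allocation has already been seen, the adjusted model should be reported as a supplementary analysis, labelled as chosen afterwards.

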### Objectives

The present RCT was designed to assess the efficacy of multimodal Ayurveda interventions in managing pain and functional disability in patients with primary osteoarthritis of the knee compared with standard care. The key secondary objectives of this study included evaluating the efficacy of the trial Ayurveda interventions on range of motion of the knee joint, the need for rescue analgesic medication, quality of life parameters, knee structural changes (ie, delay in the structural progression of osteoarthritis), proinflammatory biomarkers, and bone mineral density after 180 days. Another secondary objective was to assess the safety of multimodal Ayurveda interventions in managing osteoarthritis of the knee.

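### Within-arm significance tests share the P<.05 rule with the randomised comparison, and methods that handle several visits jointly are named only within arms

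*Protocol article*

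**What the plan says.** The primary objective is comparative: efficacy "in patients with primary osteoarthritis of the knee compared with standard care" (Objectives). The secondary efficacy objectives that follow name no comparator in their own sentence. The outcome definition does not mention the comparison either: "The primary outcome was the change in the Western Ontario and McMaster Universities Osteoarthritis Index (WOMAC) score from baseline" (Outcome Measures).

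The Statistical Methods section plans two sets of tests.

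- **Between arms:** chi-square for categorical data. For normal data, "between-group comparisons will be performed using the independent sample" *t* test. For non-normal data, "between-group comparisons will be performed using the Mann-Whitney" *U* test.
- **Within arms:** "Within-group comparisons for normally distributed data will be conducted using the paired sample" *t* "test or repeated measures ANOVA" for normal data. For non-normal data, "Within-group comparisons will be conducted using the Wilcoxon signed rank test or the Friedman test".

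One threshold covers both sets: a *P* "value <.05 will be considered statistically significant". The section does not rank the two sets and does not call the within-arm results descriptive.

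WOMAC is collected at baseline and at six later visits, on days 30 to 180 (Data Collection).

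**The concern.** A before-after test within one arm asks whether that arm changed. It cannot say whether Ayurveda did better than standard care, which is the objective. Participants enter with knee pain on most days of the last month (Study Participants) and are treated open label, so either arm may improve through natural course, regression to the mean and expectation. With both kinds of test under one threshold, a report could set a significant change in the Ayurveda arm beside a non-significant one in control and present the contrast as efficacy, although the two arms had not been shown to differ. The opening is widest for the secondary outcomes, whose objective names no comparator.

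The second part concerns the use of the visits. Repeated measures ANOVA and Friedman are the only named methods that take more than two time points together, and both are assigned to within-arm comparisons. For the randomised comparison the section names two-sample tests without adjustment for baseline and without a joint model across visits. What is at stake there is precision, not validity.

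**Working it through.** **1. What the trial is sized on.** Inputs from Sample Size: difference 20 points, pooled SD 42, two-sided α=.05, power 80%.

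n per arm = 2 × (1.960 + 0.842)² × 42² / 20² = 2 × 7.85 × 4.41 = 69.2

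The article states 69; rounding up gives 70. Power at 69 per arm is 79.9% (79.3% with the *t* distribution). The stated figure reproduces, and it belongs to a between-group *t* test on change from baseline.

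**2. Assumptions for the within-arm tests.** The article gives no SD for change within an arm and no expected change in the control arm. I assume an SD of change of 42 in each arm (the article's pooled SD), 75 analysed per arm, and the same true mean improvement μ in both arms, so that there is no treatment effect. I let μ run over 5, 10, 15 and 20 points.

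**3. Smallest significant within-arm change.** Standard error = 42/√75 = 4.85. Threshold = t(0.975; 74) × 4.85 = 1.99 × 4.85 = 9.7 points.

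**4. Chance of a significant improvement in one arm.** p is the upper-tail power of the paired *t* test, from the noncentral *t* distribution with 74 degrees of freedom and noncentrality μ/4.85. The arms are independent, so the chance that Ayurveda is significant and control is not is p(1 − p).

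| True improvement in both arms | p, Ayurveda arm significant | Ayurveda significant, control not |
|---|---|---|
| 5 | 0.173 | 0.173 × 0.827 = 0.143 |
| 10 | 0.530 | 0.530 × 0.470 = 0.249 |
| 15 | 0.863 | 0.863 × 0.137 = 0.118 |
| 20 | 0.983 | 0.983 × 0.017 = 0.017 |

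In every row the between-group test is falsely positive in 5% of trials, which is 2.5% in favour of Ayurveda.

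**5. Sensitivity to attrition.** With 69 analysed per arm the threshold is 10.1 points, and the last column becomes 0.136, 0.250, 0.139 and 0.026. The picture does not change.

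**6. Precision.** The article gives no correlation between baseline and follow-up WOMAC, so the gain from adjustment cannot be computed. Its direction can be shown. With equal variances at both times and correlation ρ, the variance of the baseline-adjusted difference relative to the change-score difference is (1 − ρ²) / [2(1 − ρ)] = (1 + ρ)/2, which is below 1 for any ρ below 1.

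**The case against.** The case on the other side is substantial, and most of it stands.

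- **The randomised comparison is planned.** A between-group test is named for every data type, and the one for normal data is the test used for the sample size. Adding within-arm tests does not change its error rate. A reader might infer that efficacy will be judged from before-after change, or that no between-group test exists. No sentence says the first, and the second is false.
- **Data are not shown to go unused.** A reader might infer that the repeated WOMAC visits drop out of the comparison between arms. Nothing confines the between-group tests to one visit; a *t* test at each visit fits the text equally well. What can be said is that no joint between-group model is named.
- **The size depends on an assumed common change.** A reader might quote about 50% for exactly one arm being significant at 10 points (2 × 0.530 × 0.470 = 0.498). That counts both directions, and it lies almost at the maximum that 2p(1 − p) can take. The pattern that would mislead in favour of Ayurveda is half of it, and at 20 points it falls to about 2%, below the 2.5% of the between-group test.
- **Model details often sit in a SAP.** True, and the absence of such details is not the point. The article does state its methods, and it assigns the joint-visit methods to the contrast that does not answer the objective.

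The objection does not remove two facts: within-arm P values carry the same threshold without any statement of their standing, and a more precise between-group analysis of data already collected is available.

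**Conclusion.** The point holds as one of interpretation and precision. The planned between-group test is valid and the trial is sized on it. The within-arm tests add P values that do not address the comparison with standard care. If both arms improve equally, they show Ayurveda significant and control not in about 14%, 25%, 12% or 2% of trials at common improvements of 5, 10, 15 or 20 points. When that pattern becomes rare, at 20 points, it is because each arm is significant with 98% probability, which is equally uninformative about the treatment difference. These figures assume an SD of change of 42 in each arm and 75 analysed per arm; the common improvement is not given in the article and is shown as a range. The loss of precision is real in direction but cannot be sized from the article. This should be changed, but it does not invalidate the trial.

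**What to change.** Issue a dated amendment before the analysing statistician is unblinded. Collection is finished and analysis is under way, so it should also record that no results by arm had been seen. It should:

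1. Replace the within-arm tests by descriptive reporting: mean change with confidence interval in each arm, without P values.
2. State that efficacy conclusions, for primary and secondary outcomes, rest only on the between-group contrast.
3. Estimate the WOMAC contrast from a mixed model for repeated measures with treatment, visit, treatment-by-visit and baseline WOMAC, and report the day-180 difference with its confidence interval. Outcome Measures names no single time point for WOMAC, so day 180, the end of treatment, has to be written in.
4. Keep the planned independent-sample *t* test as a sensitivity analysis. The mixed model uses the observed visits directly, so the amendment should say that last observation carried forward applies to the *t* test and not to the model.

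The cost is slightly more analysis work. No new data are needed and the sample size does not change.
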